## Secondary

1. To assess if access to zinc treatment for diarrhea in the home in addition to zinc treatment of diarrhea in the clinic decreases the likelihood of recurrent diarrhea episodes
2. To assess if access to zinc treatment for diarrhea in the home in addition to zinc treatment of diarrhea in the clinic leads to a reduction in the prevalence of acute respiratory infections
3. To assess if access to zinc treatment for diarrhea in the home in addition to zinc treatment of diarrhea in the clinic results in reduction in antimicrobial use
4. To assess whether treatment of diarrhea with zinc in the clinic leads to a decrease in diarrhea prevalence from baseline rates of diarrhea before introduction of zinc
5. To assess difference in zinc utilization practices in parent initiated home treatment vs clinic treatment communities
   1. frequency of use and adherence to treatment instructions
   2. who receives zinc
   3. used for what indications
6. To compare cost estimates and estimate cost benefits
7. To assess acceptability and satisfaction with a home treatment program among providers and caretakers

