### Hb 5-11 gm/dl - iron tablet or syrup and folate tablet for 14 days dosed according to age (Hb < 5 gm/dl – referral to hospital.

*Procedures for household visits.*  Field workers will visit each enrolled child every 2weeks. S/he will ask about episodes of diarrhea since the last visit as well as current episodes. S/he will also record symptoms of acute respiratory illness and malaria, as well as any health seeking and medications resulting from these illnesses (Appendix C). S/he will ask about recent or current fever and any health seeking and medications resulting from the recent or current fever. S/he will also inquire about any use of zinc in the last two weeks. The number of days of zinc and number of pills of zinc will be documented. The interviewer will ask to see the zinc blister pack and record how many pills are remaining.

*Administration of zinc*

In the villages/clusters randomized to no home zinc, parents will be instructed by the field workers to take their children to the clinic if they have diarrhea, defined as an episode having 3 or more loose or watery stools (+/-) blood in a 24 hour period. At the clinic, the child will be evaluated by a clinical officer. If the child meets the above definition of diarrhea, they will be given zinc and ORS as described below.

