*Follow-up of cases of diarrhea.* Children identified as having a new episode of diarrhea on the routine biweekly household visit or in the clinic will be visited 7 days later. Referrals will be made on these visits according the criteria listed above under G. A short questionnaire regarding ongoing symptoms and signs of illness, interim health care seeking, and possible side effects to the study medication will be administered (Appendix D). No additional zinc or ORS will be given by the field worker on follow-up visits. If the child is still having significant diarrhea at the follow-up visits, the field worker will instruct the mother to take the child back to the clinic (or to the clinic if they have not gone yet.) The child will next be visited on day 14 according to the regular weekly visit schedule.

*Definition of study outcomes.*

- 1. Diarrhea – A diarrheal day will be considered a day in which the child has 3 or more loose or watery stools. New episodes of diarrhea will be defined as at least one diarrheal day without diarrhea in the previous 72 hours. A severe diarrheal episode will be defined as an episode in which children go to the clinic to receive care for the episode.
  2. Acute Respiratory Infections.
     1. Clinical ALRI - An episode of acute lower respiratory illness (ALRI) will be defined for the home visits as a history of cough or difficulty breathing for > 2 days. An ALRI day will be considered a day that is part of an ALRI episode in which a child has cough or difficulty breathing. New episodes of ALRI will be defined as an ALRI episode without an ALRI day in the previous 72 hours. Acute respiratory infection (ARI) will include any child with cough (of any duration), difficulty breathing, or ear pain and/or discharge.
     2. Pneumonia – Pneumonia and severe pneumonia will be defined for children who visit the clinic and meet the IMCI criteria:
        1. Pneumonia in children < 5 years of age -- Cough or difficulty breathing *and* Respiratory rate > 50/minute for 2-11 month old, >40/minute for 1-4 years
        2. Severe pneumonia in children 1 month - 5 years of age

Cough or difficulty breathing and

- - - - 1. chest indrawing
        2. stridor in a calm child
        3. a general danger sign

Unable to breastfeed or drink

Vomits everything

Convulsions

Lethargy or unconscious

- 1. Malaria -
     1. Clinical malaria – History of fever in the preceding 24-48 hours as reported by the caretaker

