## Calculation and comparison of incidence rates

Incidence density rates of diarrheal disease will be calculated as number of new episodes of diarrhea per person-time. Using person-time as the denominator can incorporate information from children who are in the study for only part of the time, contributing less than 1 full year of data, due to out-migration, death or birth. 95% confidence intervals will be calculated around point estimates of incidence rates. Incidence rates for acute respiratory illness and malaria will be calculated in the same way as for diarrhea. The mean number of episodes of diarrhea will be compared between the home zinc and nonhome zinc groups using an ANOVA test accounting for repeat episodes of diarrhea within the same child, accounting for potential confounding variables, such as age and season. Potential confounders of the outcome, such as village of residence and age of the child and malaria coinfection, will be controlled for in the final model.

*Calculation and comparison of time to repeat episode of diarrhea.*

The time before a repeat episode of diarrhea in children who have their first episode of diarrhea will be compared between the home zinc and no home zinc groups. The time to a new episode of diarrhea will be measured as the number of days after the last day of the child’s first episode of diarrhea to the first day of the next episode of diarrhea in that child. This analysis will use as a Cox proportional hazards model, in which the child will be censored after the first day of their first repeat episode of diarrhea.

A secondary analysis will compare the number of repeat diarrheal episodes that occur after the first episode of diarrhea. Mean or median number of repeat episodes will be compared by t-test or Wilcoxon rank sum test depending on the distribution of episodes.

*Comparison of the effect of zinc on the treatment of diarrhea.* The mean duration of diarrheal episodes between children in the home zinc and nonhome zinc groups will be compared using ANOVA controlling for potential confounders such as age and season. Repeat episodes of diarrhea in the same children will be accounted for in the analysis. We will also analyze differences in the severity of diarrhea between groups (severe defined as visiting the clinic) and antibiotic use between groups. This will be done using logistic regression with clinic visit and use of antibiotic as the outcome variable.

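### Secondary objective 3 asks about antimicrobial use in general, but the only planned analysis is a logistic model of antibiotic use placed under diarrhoea treatment

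*Protocol*

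**What the plan says.** The third secondary objective asks whether access to zinc at home, on top of zinc in the clinic, "results in reduction in antimicrobial use". It names no indication. The second asks whether the same access "leads to a reduction in the prevalence of acute respiratory infections".

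Antibiotic use is analysed in one place only, the Data Analysis paragraph headed "Comparison of the effect of zinc on the treatment of diarrhea". After the comparison of episode duration, the plan turns to "differences in the severity of diarrhea between groups (severe defined as visiting the clinic) and antibiotic use between groups", and continues: "This will be done using logistic regression with clinic visit and use of antibiotic as the outcome variable". No unit of analysis or denominator is given. Under Definition of study outcomes, the companion outcome is tied to the episode: "A severe diarrheal episode will be defined as an episode in which children go to the clinic to receive care for the episode".

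Other outcomes get person-time denominators. For diarrhoea, "Incidence density rates of diarrheal disease will be calculated as number of new episodes of diarrhea per person-time"; respiratory illness and malaria follow the same method. Antibiotic use does not.

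On data, Procedures for household visits says field workers will record symptoms of respiratory illness and malaria at each two-weekly visit, "as well as any health seeking and medications resulting from these illnesses". The Clinic visits section provides for cotrimoxazole or amoxicillin in pneumonia, so antibiotics are also used in this trial for reasons other than diarrhoea.

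**The concern.** Objective 3 is a question about children in the two sets of villages: do those with home zinc receive fewer antimicrobials? The trial expects home zinc to act partly by preventing diarrhoea and respiratory infection. A model of antibiotic use among diarrhoea episodes asks something else, namely whether an episode, once it occurs, is treated with an antibiotic.

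Two routes to lower use are then lost. Courses avoided because a diarrhoea episode never happened leave both numerator and denominator. Courses given for respiratory illness never enter. The episodes compared are also no longer a randomised set, because the intervention may change which episodes occur. The result could show no effect when use has fallen, or an apparent rise when use is unchanged. The model is also narrower in its wording: the objective says antimicrobial, the analysis antibiotic.

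**Working it through.** **Inputs from the protocol.** The Sample size section assumes 3.6 diarrhoea episodes per child-year, lasting 3 days (plus or minus 1). The Background cites a community-randomised study in Bangladesh with 15% lower diarrhoea incidence and 7% lower incidence of acute respiratory infection in zinc villages. The protocol gives no figure for antibiotic use.

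**The plan's own figure.** 3.6 × 3 = 10.8 diarrhoea days per child-year, with range 3.6 × 2 = 7.2 to 3.6 × 4 = 14.4. This reproduces exactly.

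**Assumption.** The probability *p* of an antibiotic per diarrhoea episode is the same in both arms, between 0.1 and 0.5.

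**Courses and odds ratios with 15% fewer episodes.** Episodes fall to 3.6 × 0.85 = 3.06 per child-year. Courses per child-year = episodes × *p*. The last column treats courses as Poisson, so the chance of any use in a year is 1 − exp(−courses).

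| *p* | Clinic-only courses | Home-zinc courses | Rate ratio | Per-episode OR | Any-use-per-child OR |
|---|---|---|---|---|---|
| 0.1 | 0.36 | 0.306 | 0.85 | 1.00 | 0.83 |
| 0.2 | 0.72 | 0.612 | 0.85 | 1.00 | 0.80 |
| 0.3 | 1.08 | 0.918 | 0.85 | 1.00 | 0.77 |
| 0.5 | 1.80 | 1.53 | 0.85 | 1.00 | 0.72 |

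**Selective prevention, an extreme case.** Let *p* = 0.2 and suppose every averted episode is one that would have had no antibiotic. Courses stay at 0.72, but the per-episode probability becomes 0.72 / 3.06 = 0.235. The odds ratio is (0.235 / 0.765) / (0.2 / 0.8) = 1.23, an apparent increase with no change in total courses.

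**Respiratory courses.** Add a 7% fall in respiratory episodes, assuming 2 to 6 such episodes per child-year, an antibiotic in 0.2 or 0.5 of them, and *p* = 0.1 or 0.3 for diarrhoea (none of these is in the protocol). For example, with 4 respiratory episodes, 0.5 and *p* = 0.3:

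- diarrhoea courses averted: 1.08 − 0.918 = 0.162;
- respiratory courses averted: 2.00 − 1.86 = 0.14;
- total courses: 3.08 to 2.778, a rate ratio of 0.90;
- respiratory share of the courses averted: 0.14 / 0.302 = 46%.

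Over the whole grid the total rate ratio runs from 0.87 to 0.92, and 15% to 80% of the averted courses are respiratory. A diarrhoea-only model counts none of these.

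**The case against.** The strongest reply is that the unit is never stated. The phrase about antibiotic use between groups is not itself restricted to diarrhoea episodes, and the unit for a secondary outcome is often settled in a statistical analysis plan. This stands in part. On a child-level reading the model would see some of the effect of prevented diarrhoea, as the last column of the table shows. A reader might infer that the planned model is blind to any reduction; the document does not support that. A child-level yes/no model would still ignore repeat courses, unequal follow-up (the protocol's own reason for using person-time) and, if kept to diarrhoea, respiratory courses.

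A second reply is that objective 3 may have been meant for diarrhoea only. The baseline form (Appendix B) records antibiotics only as a treatment for diarrhoea, and the follow-up form (Appendix D) asks about other medicines taken for diarrhoea. Whether zinc displaces antibiotics within an episode is a fair question, and diarrhoea incidence is compared separately. But the objective as written carries no such limit, and the household-visit text covers medicines for other illnesses.

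Third, the size is uncertain. A reader might take the 12% detectable difference in the Sample size section as a fall in episodes. It is a difference in diarrhoea days and could arise from duration alone: 3.6 × 2.64 = 9.5 days, 12% below 10.8, with no episode averted. The Bangladesh reductions compared zinc with control villages, whereas here both arms receive zinc in the clinic. They illustrate the mechanism and do not forecast this trial.

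Finally, counting every antimicrobial could dilute the signal in an area of high malaria transmission. If antimalarials were half of all courses (an assumption) and unchanged, a 15% fall in the rest would appear as 7.5% overall. This stands, and the fix allows for it.

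**Conclusion.** The stated analysis does not match the stated objective. This is more than detail left to a statistical analysis plan, because the protocol itself chooses the model and places it under diarrhoea treatment. On the most natural reading, per episode, a 15% fall in diarrhoea-related courses goes with an odds ratio of 1.00, given equal prescribing per episode; the extreme selective case at *p* = 0.2 gives 1.23 with courses unchanged. On the child-level reading the mismatch is smaller but remains.

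The exact values rest on assumed prescribing probabilities and a borrowed incidence reduction. It would go too far to say that objective 3 is bound to be answered wrongly. The supported conclusion is that the planned model can miss or misstate a change in antimicrobial use. The change should be made, though it concerns one of seven secondary objectives and leaves the primary analysis untouched.

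**What to change.** Define the objective 3 endpoint as antimicrobial courses, for any indication, per child-time of observation, compared by randomised arm. Report antibacterials and antimalarials separately. Use person-time Poisson regression with GEE, as for the primary outcome, but name the village as the cluster: the primary-outcome text speaks only of correlation within individuals. Keep the logistic model as a supporting analysis of prescribing, and state that its unit is the diarrhoea episode.

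The cost is one analysis paragraph and probably one form change. The household-visit text plans to record medicines for all these illnesses, but the household morbidity form (Appendix C), as it appears in the document, has no medication row, so a row is needed. The clinic form (Appendix E) already lists antibiotics and antimalarials for any visit. The main downside is that counts recalled by caretakers are noisier than a yes/no answer per episode.

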## Sample size.

*Diarrhea Prevalence*.

The below calculations are for our primary study outcome of diarrhea prevalence.

Table 2a. Sample size estimates for various prevalences and reductions. Sample size table assumes a 5% reduction in diarrhea prevalence in the control group with a difference of 15% - 10% between groups.

| Difference in groups | Initial Prevalence in each group | N for each group initially/Total N | N for each group at end of trial/ Total N  (with 15% attrition) |
| --- | --- | --- | --- |
| 15% | 3.6 | 1059/2118 | 900/1800 |
| 14% |  | 1184/2368 | 1006/2012 |
| 13% |  | 1318/2636 | 1120/2240 |
| 12% |  | 1435/2870 | 1219/2438 |
| 11% |  | 1651/3302 | 1403/2806 |
| 10% |  | 3036/6072 | 2580/5160 |

Table 2b. Sample size estimates for various prevalences and reductions Sample size table assumes a 10% reduction in diarrhea prevalence in the control group with a difference of 15% - 10% between groups.

| Difference in groups | Initial Prevalence in each group | N for each group initially/Total N | N for each group at end of trial/ Total N  (with 15% attrition) |
| --- | --- | --- | --- |
| 15% | 3.6 | 1550/3100 | 1317/2634 |
| 14% |  | 1745/3490 | 1483/2966 |
| 13% |  | 1978/3956 | 1681/3362 |
| 12% |  | 2259/4518 | 1920/3840 |
| 11% |  | 2798/5596 | 2378/4756 |
| 10% |  | 4118/8236 | 3500/7000 |

We will assume 3.6 episodes per year of diarrhea in children in the study area, with an average duration of 3 days +/- 1 day. This gives a yearly prevalence of diarrhea of 10.8 days of diarrhea per child per year with a range of 7.2 to 14.4 days. We will also assume that because zinc use will increase gradually in the zinc villages as more children get diarrhea, it will take 6 months to achieve the indicated difference in diarrhea prevalence between the two groups (column 1). In the top table, it is assumed that there will be 5% reduction in diarrhea prevalence in the control group (nonhome zinc group) between the start of the study and end of the study 12 months later, due to the implementation of zinc in the clinic. The bottom table assumes that this reduction in the control group over the 12 months will be 10%.

In this repeated measures, longitudinal study design, correlation between events must be accounted for. That is, some children will be more likely to have repeated diarrheal episodes and so will contribute disproportionately to the community prevalence. To do this, sample size calculations accounted for correlation by using the generalized estimating equation (GEE) method described by Rochon (Rochon J, 1998).

Approximately 14% of enrolled participants in the morbidity surveillance study are under 5 years of age. Therefore, we would expect in a population of 25,000 enrolled participants in the 33 villages in Lwak approximately 3,000 children under 5 years. Therefore, we will have the power to detect a difference of 12% between home zinc and nonhome zinc groups, assuming a 5% decrease in diarrhea prevalence in the nonhome zinc group during the study period, or a 15% difference between the home zinc and nonhome zinc groups, assuming a 10% decrease in diarrhea prevalence in the nonhome zinc group over the study period.

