*Inclusion criteria.* All children 2 to 59 months of age in households within selected villages that are already enrolled in the IEIP morbidity surveillance project (KEMRI SSC # 985; CDC IRB # 4678) will be eligible for enrollment. Children born into the study area after the start of the study will also be eligible for enrollment after they reach 2 months of age. Recruitment and enrollment will be done by field workers working for the study, who will read the consent form to guardians of all eligible participants that explains the study.

*Exclusion criteria.* Children under 2 months of age will not be eligible for enrollment, until they reach 2 months of age as the role of zinc has not been well-studied in neonates. Children of parents who do not give written informed consent for their participation will not be enrolled.

*Randomization.* This will be a cluster-randomized study. Thirty-three villages in Asembo participating in the morbidity surveillance (see below) will be selected to participate in this study. The villages will be randomized as 16-17 villages for zinc + ORS at home and clinic villages and 16-17 villages and ORS at clinic only villages. All eligible and participating children within a village will get the same treatment. A form will be filled out to keep track of the enrollment (appendix K). See figure.

Select 33 villages in Asembo closest to Lwak clinic

Obtain community approval

of chiefs and subchiefs

Home Zinc 10 days + low osm ORS

Referral to clinic

15 villages

No home zinc or ORS

Referral to clinic

15 villages

Continue biweekly household

visits for incident and prevalent

diarrhea, ARI, fever illness

Incident diarrhea episodes

Obtain parental consent of

children < 5 years

Baseline survey of prevalence

of diarrhea, ARI, malaria

Randomly assign to home zinc

and no home zinc villages

biweekly household

visits for incident and prevalent

diarrhea, ARI, fever illness

*Baseline survey and measurements.* All enrolled households will have a baseline survey done at the beginning of the study. The survey will collect the following data (Appendix B).

- Diarrhea management and care seeking practices
- Household characteristics
- Socio-demographic characteristics of household
- Water & sanitation exposures/practices
- Knowledge & attitudes about zinc, other micronutrients
- Height & weight
- Insecticide treated bednet use
- ORS awareness/use
- Antimicrobial use

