Prevalence rates of diarrheal disease will be calculated as number of diarrheal days per person-time. Using person-time as the denominator can incorporate information from children who are in the study for only part of the time, contributing less than 1 full year of data, due to out-migration, death or birth. Curves of monthly prevalence rates of diarrhea will be calculated and plotted for home zinc and nonhome zinc villages. 95% confidence intervals will be calculated around these point estimates of prevalence rates. Because of the study design in which zinc will be given only for the treatment of diarrhea, the preventive effects of zinc will likely become more apparent with time as more children receive zinc. Therefore, initially the prevalence will be the same. With time, the prevalence might diverge between the study groups. Prevalence rates over time between the home zinc and nonhome zinc groups will be compared using Poisson regression applying the generalizing estimating equation (GEE) technique to account for the repeated measures design and control for correlation of diarrheal days among individuals. The Wald test will be used to evaluate the parameter that estimates the effect of treatment group. Statistical significance will be considered at the 0.05 level. Potential confounders of the outcome, such as village of residence and age of the child , will be controlled for in the final model.

Prevalence rates for clinically suspected acute respiratory illness based on the caretakers reports every 2 weeks will be calculated in the same way as for diarrhea.

In addition, we will analyze the cumulative dose effect (total number of zinc days) on the prevalence of diarrhea among individuals in the zinc villages using poisson regression with total number of zinc days as the independent variable.

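### The sample size allows for correlation within a child but not for village clustering, so the stated power to detect 12% and 15% is unsupported for this 33-village design

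*Protocol*

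**What the plan says.** On the design, the Randomization paragraph of the protocol (Study design) states: "This will be a cluster-randomized study". It continues: "The villages will be randomized as 16-17 villages for zinc + ORS at home and clinic villages", with a similar number in the clinic-only arm, and "All eligible and participating children within a village will get the same treatment".

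On the sample size, the section of that name starts from a rate: "We will assume 3.6 episodes per year of diarrhea in children in the study area". It takes 10.8 diarrhoea days per child-year and tabulates numbers of children in Tables 2a and 2b. The correlation it sets out to handle is described in these words: "That is, some children will be more likely to have repeated diarrheal episodes and so will contribute disproportionately to the community prevalence". A repeated-measures GEE sample-size method is cited for that purpose. The section then expects about 3,000 children under five in the 33 villages and concludes: "Therefore, we will have the power to detect a difference of 12% between home zinc and nonhome zinc groups" if prevalence in the clinic-only arm falls by 5%, or 15% if it falls by 10%.

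The section gives no village ICC, between-village CV or design effect. The number 33 appears only as the source of the child count. The planned primary analysis, under the heading on prevalence rates, reads the same way: GEE is there for repeated measures and correlation among individuals, and village of residence is listed as a potential confounder. On the error rate it says: "Statistical significance will be considered at the 0.05 level". No power value is given.

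**The concern.** When whole villages are randomised, variation between villages goes straight into the variance of the treatment contrast, and adding children within villages does not remove it. A sample size that models only within-child correlation is a sample size for individually randomised children with repeated measures. Reading a detectable difference from it for 16 versus 17 villages is therefore not justified.

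The August 2006 rationale says the Ministry of Health wants the result to help decide on community roll-out. If the difference is not significant, readers will judge it against the stated sensitivity of 12% to 15%. If that sensitivity was never worked out for this design, an inconclusive result could be taken as evidence against a benefit of that size.

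**Working it through.** **1. The plan's own figures.** The attrition step reproduces in all 12 rows, rounding up: for example 1,219 / 0.85 = 1,434.1 (printed 1,435) and 1,317 / 0.85 = 1,549.4 (printed 1,550). The numbers before attrition cannot be reproduced, because power, within-child correlation and number of periods are not stated. For scale, take a plain two-sample Poisson formula with assumed 80% power, two-sided 0.05, a control rate of 3.6 × 0.95 = 3.42 and a zinc rate of 3.42 × 0.88 = 3.01. This gives (1.96 + 0.84)² × (3.42 + 3.01) / (3.42 − 3.01)² ≈ 300 per arm, against 1,219 printed.

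**2. Margin in the printed rows.**
- Table 2a, 12%: 2,870 needed and about 3,000 expected, so 3,000 / 2,870 = 1.045.
- Table 2b, 15%: 3,100 needed, which is 100 more than expected before any village inflation.

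**3. Village ICC that uses up the margin.** Children per village m = 3,000 / 33 = 90.9, and DE = 1 + (m − 1) × ICC. Setting DE = 1.045 gives ICC = 0.0453 / 89.9 ≈ 0.0005.

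**4. Design effect on the printed numbers.** The ICCs are assumed, as the protocol gives none.

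| ICC | DE | Children for 12% row (2,870 × DE) | Children for 15% row, Table 2b (3,100 × DE) |
|---|---|---|---|
| 0.005 | 1.45 | 4,160 | 4,494 |
| 0.01 | 1.90 | 5,450 | 5,887 |
| 0.02 | 2.80 | 8,031 | 8,674 |

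**5. Cluster-level calculation, independent of the tables.** From the protocol: 10.8 days in control, so 10.8 × 0.88 = 9.504 under a 12% difference (contrast 1.296); 16 and 17 villages; alpha 0.05. Assumed: a two-sided test, child variance 78 (SD 8.8, CV about 0.82), no attrition, t test on village means with 31 df. The variance of a village mean is (k × rate)² + 78 / 90.9, and 78 / 90.9 = 0.858.

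| k | Variance, control / zinc | SE of contrast | 1.296 / SE | Power for 12% |
|---|---|---|---|---|
| 0 | 0.858 / 0.858 | 0.323 | 4.02 | 97% |
| 0.09 | 1.803 / 1.590 | 0.454 | 2.85 | 79% |
| 0.15 | 3.482 / 2.890 | 0.623 | 2.08 | 52% |
| 0.25 | 8.148 / 6.503 | 0.944 | 1.37 | 26% |

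**6. Comparing steps 4 and 5.** With this variance, k = √(78 × ICC) / 10.8, so ICC 0.005, 0.01 and 0.02 correspond to k of about 0.058, 0.082 and 0.116. Power for 12% is then about 91%, 82% and 67%. Step 4 says that 3,000 children fall short at all three ICCs; step 5 gives more than 80% power at the first two. The methods start from different places. Step 4 multiplies numbers that already carry an unstated within-child inflation, while step 5 rests on an assumed child variance that yields 97% power with no village variation. They are two views of an unknown quantity and should not be merged into one figure.

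**The case against.** Four things can be said for the plan.

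*The GEE method might have included villages without saying so.* The printed 1,219 is about four times the simple Poisson figure of 300, so some large inflation is in there. But the section attributes the correlation to children with repeated episodes, and the analysis section speaks of correlation among individuals. Nothing assigns any part of it to villages. This does not stand.

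*The point could be left to the statistical analysis plan.* The power claim is made in the protocol, from tables printed there. A later document cannot change what those tables were computed for.

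*Between-village variation may be small.* This stands. The protocol describes a culturally homogeneous area, with the study sited within 4.25 km of one hospital. That does not establish a low k, but nothing in the protocol establishes k of 0.15 to 0.25 either. A more favourable rate-based calculation that ignores extra variation between children (3.6 episodes a year, 15% attrition) gives 87% power for 12% at k = 0.10 and 61% at k = 0.15. Nor can village variation be assumed to dominate: under the inputs of step 5, the child sampling component (0.858) exceeds the village component at ICC 0.005 (0.39) and at ICC 0.01 (0.78).

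*A revised detectable difference cannot be read from the printed tables.* This also stands. A reader might scale 12% by the square root of the design effect, but the tables do not follow that law: the 12% row would predict 1,435 × (12 / 15)² ≈ 918 per group at 15%, where 1,059 is printed. At DE 1.45, even the 14% row needs 2,368 × 1.45 ≈ 3,430 children, more than the 3,000 expected.

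**Conclusion.** The omission is real and can be seen in the text: villages are randomised, and no village-level variance enters the sample size. The 12% and 15% statements are therefore unsupported for this design. Two results need no assumed ICC: the 12% row has a 4.5% margin, and the 15% row of Table 2b exceeds the expected number of children. That an ICC of about 0.0005 removes the margin follows from 91 children per village.

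The size of the loss is unknown. The design effects of 1.45 to 2.80 rest on assumed ICCs, and the powers of 79%, 52% and 26% rest on an assumed k and a child variance of 78.

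A reader might infer that the trial lacks power for 12% to 15% or could not have detected such an effect. The documents do not support that: with k of about 0.09 or less, 33 villages would give roughly 80% power or more for 12% under the assumptions above. The sound conclusion is that the stated power has not been shown.

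**What to change.** Estimate the between-village CV or ICC of diarrhoea days from the biweekly surveillance, which already records days of symptoms in these 33 villages. Recompute the detectable difference with a cluster-randomised formula for 16 versus 17 villages. State alpha and whether the test is two-sided, power, the ICC or k with its source, and children per village after attrition (with 15% loss, 90.9 × 0.85 ≈ 77). Replace the 12% and 15% statements with the result, whether it confirms them or not.

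The recalculation needs one set of counts. The study flow chart shows 15 villages per arm and the abstract gives about 1,300 children (about 39 per village), so both should be reconciled with the Randomization and Sample size text first.

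The cost is one calculation from data in hand and possibly a less favourable stated figure. It requires no extra villages, enrolment or procedures.
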